### Sample Size Calculation

A sample size determination was conducted for the main outcome variable. Hypothesizing an AUC for overall pain in the first 24 hours of 144 patients in group B and 120 patients in group A, a common SD of 60, 140 patients per group will be necessary to achieve 92% power with an alpha error of 5% with a 2-sided *t* test for independent samples.

On the basis of preliminary results of a pilot study conducted at the Catania center, we expect to lose no more than 5% of patients because of surgery durations >90 min; thus, we plan to enroll 300 patients to be allocated in the ratio 1:1 in 2 groups.

### Interim Analysis

No interim analysis is planned.

### Randomization: Sequence Generation, Allocation Concealment Mechanism, and Implementation

#### Sequence Generation

Allocation sequence to groups A and B will be obtained using the “ralloc” module in Stata 14 (StataCorp LLC, College Station, Texas), with blocks of variable size (4-6-8), and stratified by participating center and type of surgery (hysterectomy). The algorithm for sequence generation will be maintained by the study statistician and will not be communicated to any additional study staff.

#### Allocation Concealment Mechanism

The study statistician will prepare the appropriate number of numbered, opaque, sealed envelopes for each center. These will be maintained at each center by an appropriately trained research nurse. At the time of anesthesia induction, the surgical nurse will open the relevant envelope, and the anesthesiologist will proceed to the allocated treatment.

### Data Collection and Management

Study data on the primary and secondary outcomes will be collected from clinical charts and by dedicated data personnel using Research Electronic Data Capture electronic data capture tools [27]. The electronic database will be built by bioinformatics experts and will include built-in quality checks for key variables.

### Statistical Analysis

#### Statistical Methods for Analyzing Primary and Secondary Outcomes

The primary endpoint (AUC for pain) will be compared by Student *t* test. *P* value <.05 will be considered significant. Descriptive statistics will be obtained for all variables assessed in the study population. Mean and SD will be used for normally distributed variables, and mean and interquartile range will be used for skewed distributions and proportions for categorical variables. Whenever relevant, 95% CIs will be calculated.

For group comparisons, Student *t* test (rank-sum test or Mann–Whitney test for skewed distributions) will be used for quantitative variables (analysis of variance or Kruskal-Wallis for >2 groups, respectively) and Pearson chi-square test (Fisher exact test where appropriate) for categorical variables. Two-tailed tests will be used in all cases. *P* value <.05 will be considered significant.

Generalized mixed models will be used to assess differences between groups in endpoints measured at several time points.

A detailed statistical analysis plan will be developed after the first 40 patients have been enrolled.

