### Trial Design

This will be a multicenter, randomized controlled trial with a superiority design. Patients will be randomly allocated in the ratio 1:1 to one of two parallel groups with stratification by type of surgery and clinical center.

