### Setting and Data Collection Locations

Participating centers will be selected among those where laparoscopic and/or robotic gynecologic surgery is standard of care, performing at least 100 laparoscopic hysterectomies per year (or 200 laparoscopic procedures per year), with sampling distributed geographically across Italy. Both university and general hospitals can participate. At each center, a single surgeon (and team) and a single anesthesiologist (and team) will be involved.

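### The primary AUC is tested without the two factors that stratify randomisation; if centre or surgery type predicts pain, the test is conservative and its confidence interval too wide

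*Protocol article*

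**What the plan says.** Under Trial Design, the protocol article states: "Patients will be randomly allocated in the ratio 1:1 to one of two parallel groups with stratification by type of surgery and clinical center". Sequence Generation gives the method: "with blocks of variable size (4-6-8), and stratified by participating center and type of surgery (hysterectomy" yes or no). Allocation is therefore balanced, up to incomplete blocks, within each combination of centre and surgery type.

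Statistical Methods for Analyzing Primary and Secondary Outcomes fixes the primary comparison: "The primary endpoint (AUC for pain) will be compared by Student" t test. No covariate or stratum is named. The Sample Size Calculation section rests on the same unstratified two-sample t test.

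Three other statements bear on the point:

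- Generalized mixed models are planned for endpoints measured repeatedly. Their terms are not listed.
- Methods for Any Additional Analyses adds analyses stratified by type of intervention and analyses that consider uterus volume. Both are additional to the main analysis, and neither involves centre.
- A detailed analysis plan is to be written once 40 patients have been enrolled.

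**The concern.** Blocking within strata makes the arms alike in centre and surgery type by design. Differences in pain between centres, or between hysterectomy and adnexal surgery, then contribute almost nothing to the chance variation of the treatment difference. The t test does not use this. Its pooled SD still includes the between-stratum variation, so the standard error is larger than the real sampling error.

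The protocol gives grounds to think the factors may be prognostic. The procedures range from cystectomy to hysterectomy. The choice of premedication drugs is left to the anesthesiologist. On staffing, Setting and Data Collection Locations says: "At each center, a single surgeon (and team) and a single anesthesiologist (and team) will be involved". The authors' choice of these two factors for stratification points the same way.

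At stake is whether the nominal 5% test and 95% interval have those properties, and whether precision that the design can provide is used. The interval matters here because the Introduction and Discussion ask whether the benefit is clinically significant, not only whether it exists.

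**Working it through.** **Inputs.** The Sample Size Calculation section gives "Hypothesizing an AUC for overall pain in the first 24 hours of 144 patients in group B and 120 patients in group A" (144 and 120 are read as AUC values), so the difference is 24. It then states: "a common SD of 60, 140 patients per group will be necessary to achieve 92% power". The t test is two-sided at the 5% level. R² is not in the document and is varied as an assumption.

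**1. The plan's own figure.** The standard error is 60 × √(2/140) = 7.17. Power by the normal approximation is Φ(24/7.17 − 1.96) = Φ(1.387) = 91.7%. The noncentral t distribution gives 91.5%. The stated 92% is reproduced. Allowing for 5% loss, 280/0.95 = 295, which 300 covers.

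**2. True sampling error under stratified allocation.** Let R² be the share of within-arm AUC variance explained by the two factors, and take 60 as the overall SD, since the protocol enters it into an unstratified test.

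- Standard error used by the t test: 7.17, whatever R² is.
- Actual sampling error, which an adjusted model estimates: 7.17 × √(1 − R²).
- Real alpha of the t test: 2 × [1 − Φ(1.96/√(1 − R²))].
- Excess interval width: 1/√(1 − R²) − 1.
- Unadjusted power: Φ[(24 − 1.96 × 7.17)/(7.17 × √(1 − R²))].
- Adjusted power: noncentral t with SD = 60 × √(1 − R²).

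| Assumed R² | Actual SE | Real alpha, t test | 95% CI half-width, t test v adjusted | Excess width | Power, t test | Power, adjusted |
|---|---|---|---|---|---|---|
| 0 | 7.17 | 5.0% | 14.1 v 14.1 | 0% | 91.7% | 91.5% |
| 0.05 | 6.99 | 4.4% | 14.1 v 13.7 | 2.6% | 92.3% | 92.8% |
| 0.10 | 6.80 | 3.9% | 14.1 v 13.3 | 5% | 92.8% | 94.0% |
| 0.20 | 6.41 | 2.8% | 14.1 v 12.6 | 12% | 93.9% | 96.2% |
| 0.30 | 6.00 | 1.9% | 14.1 v 11.8 | 20% | 95.1% | 97.9% |

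In the first row, 91.7% and 91.5% differ only because one column uses the normal approximation and the other the noncentral t.

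**3. The gain expressed as patients, at R² = 0.20.** To match the adjusted interval width, the unadjusted analysis needs 1/(1 − 0.20) = 1.25 times the patients, or 175 per arm. To match the adjusted power it needs fewer. The unadjusted power formula reaches the adjusted power at about 158 per arm, and 158/140 = 1.13.

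**4. Simulation check.** The settings were 20 strata (assumed), blocks of 4, 6 and 8, 280 patients and 3000 runs per setting. At R² = 0.10, 0.20 and 0.30:

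- Type I error of the t test was 3.7%, 2.3% and 2.2%.
- Type I error of the adjusted analysis was 4.4%, 4.0% and 5.1%.
- Power, unadjusted against adjusted, was 92.3% v 93.4%, 93.8% v 96.2% and 94.8% v 97.9%.

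The simulation error on a 5% rate is √(0.05 × 0.95/3000) = 0.4 percentage points. The runs therefore support the direction and rough size, not the last digit. At R² = 0 the mean standard errors were 7.16 unadjusted and 7.18 adjusted, so needless adjustment cost almost nothing.

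**The case against.** **The effect is conditional.** The document gives no R², no intraclass correlation and no number of centres. Anaesthesia and postoperative analgesia are largely standardised, so a large centre effect on pain cannot be presumed. This stands, and it is why the table starts at zero.

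**An unadjusted t test is valid, and the sample size was built on it.** This also stands. A reader might infer that the trial is underpowered or its result biased. The documents do not support that. With 60 as the overall SD, the t test's power stays at about 92% or rises with R². Its type I error is below 5%, not above it. What is forgone is about 1 to 3 points of additional power at R² of 0.10 to 0.30.

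**The gain is easily overstated.** A reader might take the 25% more patients at R² = 0.20 as the price in power. That figure applies to interval width only; for power it is about 13%.

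**Surgeon satisfaction.** A reader might extend the point to surgeon satisfaction, with centre as a rater effect. Satisfaction is scored repeatedly during surgery, so it falls under the mixed models, whose terms are not given. One rater per centre is itself an inference, because the protocol refers to a surgeon and team.

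**The analysis plan may settle it.** Covariates are often listed there. Here, however, the protocol does not leave the primary test open: it names one. Adding strata later would change a stated primary method after enrolment has begun. The additional analyses by type of intervention do not alter the primary test and do not involve centre.

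**Conclusion.** The point holds as an efficiency and interval-coverage issue. The randomisation uses centre and surgery type, and the stated primary test uses neither. If the two factors explain 5% to 20% of AUC variance, the real alpha is about 4.4% to 2.8% and the interval about 2.6% to 12% too wide. The power forgone is about 0.5 to 2.3 points. If they explain none, nothing is lost.

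These figures assume 140 analysed patients per group, a difference of 24, an overall SD of 60, near-complete balance within strata and the stated R² values. The direction does not depend on the exact R²; the size does. The mismatch does not invalidate the trial. It should be corrected because the remedy is cheap and brings the analysis into line with the allocation.

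**What to change.** In Statistical Methods for Analyzing Primary and Secondary Outcomes, replace the primary t test with a linear model of AUC on treatment, centre and surgery type (hysterectomy yes/no). Report the adjusted mean difference with its 95% confidence interval. Keep the Student t test as a sensitivity analysis. Make the change before the analysis plan is written, so that both documents name the same primary method.

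The cost is one degree of freedom per additional centre plus one for surgery type. The number of centres is not stated. With 20 centres, for example, residual degrees of freedom would fall from 278 to 278 − 19 − 1 = 258, and the critical t value would stay at 1.969 to three decimals. If many centres are small, centre may be fitted as a random effect. No new data are needed, and the enrolment target of 300 is unchanged.

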Surgeon satisfaction	Likert scale 1-5; neck strain, back strain, visual acuity, overall satisfaction	Questionnaire: every 15 min from first laparoscopic view until removal of laparoscopes at the end of surgery or up to 8 hours from the first score.
Hemodynamic stability during surgery	Yes/no	Determined clinically: systolic and diastolic blood pressures, total diuresis, need for catecholamines, etc
Respiratory stability during surgery	Yes/no	Determined clinically by monitoring PaO_2_, PaCO_2_, etc
Duration of surgery from first access to umbilical incision closure	Measured in minutes	N/A^c^
Time from administration of NMB^d^ antagonist to awakening	Measured in minutes	N/A
PONV^e^	AUC of NRS 0-10 in the first 24 hours	N/A
Time from surgery to discharge	Measured in days	Postanesthesia Discharge Scoring: ≥2 assessments > 8.5 hours apart
Postoperative evaluation	Composite endpoint	Telephone questionnaire [26]
Direct costs	Number, description, and type of drug; type of intervention (International Classification of Diseases, Ninth Revision, ICD9 code); year; operating theater time; NMB reversal time (end of surgery to extubation); type and number of personnel present; anesthesia; presence/absence of postoperative residual curarization (PORC); prophylactic therapy for PORC; rescue therapy for PORC; PACU^f^ stay, yes/no; PACU stay duration, minutes; PACU stay >60 min, yes/no; intensive care unit admission, yes/no; with immediate extubation?, with early extubation?, with delayed extubation?	These data will be registered on a dedicated monitoring form for each patient.
Indirect costs	Absence from work; lost productivity; QoL^g^	EuroQoL-5 dimensions questionnaire (possibly other appropriate instruments)

^a^AUC: area under the curve.

^b^NRS: numerical rating scale.

^c^N/A: not applicable.

^d^NMB: neuromuscular blockade.

^e^PONV: postoperative nausea and vomiting.

^f^PACU: postanesthesia care unit.

^g^QoL: quality of life.

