#### Secondary Outcomes

Secondary outcomes are summarized in Table 2.

Procedures lasting >90 min from first access to umbilical incision closure will be excluded from the analysis. The surgeon will rate surgical conditions every 10 min during the procedure and again at the end, using a 5-point scale (1=excellent, 2=good, 3=acceptable, 4=poor, and 5=inadequate).

In the economic analysis, direct costs will be based on operating and patient recovery times in the context of each hospital center, including time in the operating room and PACU and costs for the professionals monitoring the patient before extubation and resumption of spontaneous respiration. Indirect costs will be captured with the EuroQOL-5 dimensions quality of life questionnaire, lost productivity, and absence from work.

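### The rule for skewed variables pairs the mean with the interquartile range and, read literally, tests skewed costs by ranks instead of comparing mean cost per patient

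*Protocol article*

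**What the plan says.** The section *Statistical Methods for Analyzing Primary and Secondary Outcomes* sets one general rule for quantitative variables. Normally distributed ones get mean and SD and a Student t test. For the others, "mean and interquartile range will be used for skewed distributions" and the comparison is by "rank-sum test or Mann–Whitney test for skewed distributions". No separate method is named for costs. The section adds that 95% CIs will be given where relevant and that a detailed analysis plan will follow once 40 patients are enrolled.

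Direct and indirect costs are a listed secondary objective, and the Introduction names cost-effectiveness among the open questions. Costs are described in two places:

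- **Text under *Secondary Outcomes*:** "direct costs will be based on operating and patient recovery times in the context of each hospital center". The components it goes on to name are theater time, PACU time and staff. Drugs are not mentioned. "Indirect costs will be captured with the EuroQOL-5 dimensions quality of life questionnaire", and the same sentence goes on to name lost productivity and absence from work.
- **Table 2:** the first direct-cost item is "Number, description, and type of drug". Theater time, personnel, treatment of residual curarization, PACU stay and intensive care follow. "These data will be registered on a dedicated monitoring form for each patient". Quality of life is listed under indirect costs beside work absence and lost productivity.

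**The concern.** Two parts of the general rule do not serve their purpose.

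First, the mean and the interquartile range do not describe the same feature of a skewed distribution. The quartiles bracket the median, and the mean can lie near or even beyond the upper quartile. As printed, the rule covers every skewed variable in the trial, such as theater and PACU times.

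Second, per-patient costs are usually right-skewed, so the literal rule sends them to a rank-sum test. That test asks whether a patient in one arm tends to rank above a patient in the other. A hospital's spend is the number of patients times the mean cost, and a cost-effectiveness ratio is also built on means. The rank-sum P value can therefore disagree with the comparison that the cost objective calls for.

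A smaller matter is that the text and Table 2 do not describe direct costs in the same way. The item that the text leaves unmentioned, drugs, differs between the arms by protocol.

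**Working it through.** **The plan's own figure.** The article states no figure for the cost analysis. Its only power statement concerns the primary AUC: difference 144 − 120 = 24, SD 60, 140 per group, two-sided 5%. The standard error is 60 × √(2/140) = 7.17, and 24/7.17 − 1.96 = 1.39, which gives 91.7% power (91.5% by noncentral t). The stated 92% reproduces. It has no bearing on this point beyond supplying 140 per arm for what follows.

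**Assumptions.** Costs are lognormal with log-SD σ_A (intervention) and σ_B (control), and the control mean is 1000 units. None of this is in the article. The log-SDs are chosen only to show a range.

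**Formulas.**
- Mean = median × exp(σ²/2).
- The rank-sum test responds to P(A < B) = Φ[(ln median_B − ln median_A)/√(σ_A² + σ_B²)]. The mean does not enter except through the median.

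**Missing a difference.** With equal medians and log-SDs of 0.6 and 0.4, the mean ratio is exp(0.18 − 0.08) = 1.105, so A is 10.5% dearer. Here P(A < B) = 0.5, and the rank-sum test rejects in about 5% of trials. A Welch test on means rejects in about 30%.

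**Equal means, unequal spread.** For log-SDs 0.8 and 0.4 the medians are 1000 × exp(−0.32) = 726 and 1000 × exp(−0.08) = 923. Then P(A < B) = Φ(0.24/0.894) = 0.61, although the mean costs are identical. Simulated rejection rates (140 per arm, 3000 runs):

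| log-SD A, B | Rank-sum | Welch on means |
|---|---|---|
| 0.5, 0.5 | 5% | 5% |
| 0.7, 0.5 | 35% | 5% |
| 0.8, 0.4 | 86% | 6% |
| 1.0, 0.5 | 97% | 6% |

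**Reversing a difference.** Let A's mean be 1100 and B's 1000.
- Log-SDs 0.8 and 0.4: medians 799 and 923, P(A < B) = Φ(0.145/0.894) = 0.56. The rank-sum test declares A cheaper in 47% of trials.
- Log-SDs 1.0 and 0.5: medians 667 and 882, P(A < B) = Φ(0.280/1.118) = 0.60. It declares A cheaper in 82%.

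**Equal spread.** With a 10.5% mean difference and the same log-SD in both arms, rank-sum and Welch reject in 54% and 53% of trials (log-SD 0.4), 36% and 34% (0.5), and 27% and 24% (0.6). The choice of test then hardly matters.

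**Drug quantity.** The stated reversal doses are 4 and 2 mg/kg, a difference of 2 mg/kg. At assumed weights of 50, 65 and 80 kg this is 100, 130 and 160 mg per patient, always more in the intervention arm. The article gives no price, so the amount in money cannot be computed.

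**The case against.** The strongest reply has four parts.

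- **Unequal spread is assumed.** Nothing in the article says that the arms differ in cost spread or shape, and with equal spread the rank-sum test performs like a test of means. This stands. It limits the claim to what can happen.
- **Switching to means does not buy much power.** In the equal-median example a test of means finds the 10.5% difference in only about 30% of trials. This also stands. The reason to switch is that the estimate then answers the cost question.
- **The article leaves room.** It foresees 95% CIs, its printed rule reports a mean even for skewed variables, and the later analysis plan may set a cost method. That softens the point. The rule as printed still makes no exception for costs, and a later plan could inherit it.
- **Costs are secondary.** This is correct. The primary AUC has its own t test.

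A reader might go further and infer that drugs will not be costed. The documents do not support that: Table 2 puts drugs first among the direct-cost items, and the list of times and staff in the text is introduced as inclusive, not exhaustive. A reader might also infer that EQ-5D alone stands in for indirect costs. The sentence continues with lost productivity and work absence, and Table 2 lists both. What remains in each case is a difference in wording and labeling.

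**Conclusion.** The point holds in two respects. The pairing of mean with interquartile range is a plain error, probably a slip for median. The rank-sum rule, read literally, is unsuited to costs because it does not test the mean difference per patient.

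The consequence of the second is conditional. Under assumed lognormal costs with unequal spread, the test can miss a mean-cost difference, find one where none exists (35% to 97% of trials), or point the wrong way (47% or 82%). With equal spread it does no harm. It would go too far to say that the plan will give the wrong cost answer, because no cost mean, SD or price is available to show that.

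The mismatch between the cost text and Table 2, and the placing of EQ-5D under indirect costs, are minor consistency matters. The primary analysis and the sample size are unaffected.

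**What to change.** 1. In the statistical methods section, replace *mean* by *median* in the summary for skewed variables.
2. Exempt costs from the skewed-variable rule, both summary and test. Report the arithmetic mean cost per patient in each arm and the mean difference with a bootstrap or gamma-model 95% CI.
3. Under *Secondary Outcomes*, state that the direct-cost comparison prices every direct-cost item of Table 2, including the quantity of blocking and reversal drugs.
4. Label EQ-5D as a quality-of-life outcome reported beside indirect costs, and keep work absence and lost productivity as the indirect-cost items.

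The cost is a few sentences and a short analysis script. Drug items are already on the per-patient monitoring form. The one thing to confirm is that the form records drug amounts, since Table 2 names number, description and type but not quantity in mg.

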**Conclusions:**

This study is designed to confirm the reported benefits of postoperative pain and provide additional data needed to address questions regarding the effects of this intervention on operating theater management and direct and indirect costs. Strengths of this protocol include the large sample size distributed among diverse institutions across the Italian territory and the collection and analysis of data on numerous secondary objectives. Limitations include the possible introduction of bias because the surgeon and anesthesiologist are not blinded to the intervention.

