## Methods

### Study Objectives

The primary objective of this study was to assess the superiority of anesthesia with deep NMB with pneumoperitoneum 8 mm Hg over moderate blockade with pneumoperitoneum 12 mm Hg, in terms of overall pain 24 hours after waking in adult women undergoing pelvic surgery for hysterectomy or benign adnexal diseases.

Secondary objectives will be to assess differences between the 2 groups in terms of:

Patient relaxation quality during surgeryNeed for administration of additional NMB agents based on intraoperative train-of-four (TOF)Surgeon satisfaction (Likert scale: 1=impossible to proceed, 2=insufficient, 3=sufficient, 4=good, and 5=excellent) on each of the following:neck strainback strainvisual acuityoverall satisfactionHemodynamic stability during surgery, determined clinically by monitoring systolic and diastolic blood pressures, electrocardiogram and, in part, by capnography.Respiratory stability during surgery, determined clinically by monitoring ventilation parameters: O_2_ saturation, end-tidal CO_2_, and CO_2_ insufflation pressure; tidal volume; positive end-expiratory pressure; inspiratory-to-expiratory ratio; fractional O_2_ percentage; and blood gases.Direct and indirect costsDuration of surgery (from first access to umbilical closure, in minutes)Time to awakening (from induction to awakening, in minutes)Time from the end of the surgery to awakening (modified Wilson sedation scale)Time to discharge from postanesthesia care unit (PACU; from induction to discharge, in minutes)Time in operating theater stay from entry to discharge to PACU or wardPostoperative nausea and vomiting (PONV), at the same time points as for pain, using a 0 to 10 numerical rating scale (NRS)Time to discharge, evaluated with the Postanaesthetic Discharge Scoring System [26]

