## Discussion

Laparoscopic surgery provides benefits that include less bleeding, faster recovery, and shorter hospital stays. However, it is performed in a restricted space that may limit the surgeon’s view and range of motion. Higher CO_2_ insufflation pressure provides more insufflation volume [28] and improves surgical field visibility [29] but is associated with increased postoperative side effects [1]. During laparoscopic procedures, maintaining deep NMB, compared with moderate NMB, is associated with improved surgical conditions, as reviewed in Madsen and colleagues’ study [17]. NMB also improved surgical conditions when suturing the abdominal fascia [18]. However, the advantages of deep NMB in laparoscopic surgery are not well established, and questions remain regarding the clinical significance of the improvements, safety, and cost-effectiveness.

This study may confirm the reported benefits for postoperative pain and provide the additional data needed to address questions regarding the effects of this intervention on operating theater management and direct and indirect costs.

Strengths of this protocol include the large sample size and the participants being distributed among diverse institutions across the Italian territory, which will increase the generalizability of the results. The study will provide a comprehensive picture of the effect of and the collection and analysis of data on numerous secondary objectives, including an analysis of direct and indirect costs, to determine the overall effect of the intervention. Limitations include the possible introduction of bias because the surgeon and anesthesiologist will not be blinded to the intervention. However, potential bias will be reduced through blinding of the nurse who will assess the primary outcome (ie, the AUC of overall pain during the first 24 hours after surgery measured on an NRS of 0-10). Moreover, the randomization sequence will be generated centrally and allocation concealed in opaque, sealed envelopes until the time of anesthesia induction.

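### The protocol applies one flat P<.05 significance rule to about 26 secondary comparisons (about 31 with those listed only in the objectives), with no ordering, correction or exploratory label

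*Protocol article*

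**What the plan says.** Under Statistical Methods for Analyzing Primary and Secondary Outcomes, the primary analysis is stated first: "The primary endpoint (AUC for pain) will be compared by Student *t* test", with P<.05 as its threshold. A second paragraph then turns to comparisons in general: "For group comparisons, Student *t* test (rank-sum test or Mann–Whitney test for skewed distributions) will be used for quantitative variables", with chi-square or Fisher tests for categorical variables. It closes with "Two-tailed tests will be used in all cases. *P* value <.05 will be considered significant". A further sentence adds repeated-measures analyses: "Generalized mixed models will be used to assess differences between groups in endpoints measured at several time points".

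Study Objectives introduces a long list with "Secondary objectives will be to assess differences between the 2 groups in terms of", and Table 2 gives an overlapping but not identical list. The section on additional analyses adds analyses stratified by type of intervention and analyses that consider uterus volume.

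On the purpose of this material, the Discussion counts the numerous secondary objectives as a strength, "including an analysis of direct and indirect costs, to determine the overall effect of the intervention". The abstract's conclusions say the study is meant to "provide additional data needed to address questions regarding the effects of this intervention on operating theater management and direct and indirect costs".

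The SAP is still to come: "A detailed statistical analysis plan will be developed after the first 40 patients have been enrolled".

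**The concern.** The protocol does not leave open how secondary results will be judged. It states the threshold a second time, in a paragraph that sets no outcome apart, in a section headed as covering both primary and secondary outcomes. An analyst who follows it would call any secondary comparison with P<.05 significant, whatever the primary showed and however many comparisons were made.

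At stake is the reading of the results. Nine secondaries concern pain: rescue use, pain at three sites, maximum pain and its timing. With a null primary, each would still offer a full-alpha route to a statement about pain. The same holds for surgeon satisfaction, operating times and costs, on which the article expects to draw conclusions. Nothing in the text tells a reader to treat such findings as hypothesis-generating.

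**Working it through.** **1. The plan's own error figure.** The 5% alpha appears under Sample Size Calculation and refers to the main outcome variable only. With means 144 and 120, SD 60 and 140 per group, the noncentrality is (24/60) × √(140/2) = 3.347. Power is Φ(3.347 − 1.960) = 91.7% (91.5% by the exact noncentral t), which agrees with the stated 92%. There is one primary endpoint, one contrast and no interim analysis, so its 5% stands. The article states no error figure for the secondaries.

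**2. Count from Table 2.**

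| Outcome | Comparisons | Running total |
|---|---|---|
| Rescue needed | 1 | 1 |
| Rescue doses, 24 h and 48 h | 2 | 3 |
| Pain AUC at three sites | 3 | 6 |
| Maximum pain, time to maximum, time to pain below 4 | 3 | 9 |
| Movement; movement requiring recurarization | 2 | 11 |
| Surgeon satisfaction, four items | 4 | 15 |
| Hemodynamic and respiratory stability | 2 | 17 |
| Duration of surgery; antagonist to awakening | 2 | 19 |
| PONV AUC, time to discharge, telephone composite | 3 | 22 |
| Direct costs, taken as one | 1 | 23 |
| Indirect costs, three items | 3 | 26 |

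Study Objectives adds five: additional blocking agent, induction to awakening, end of surgery to awakening, discharge from PACU, and theater stay. The total is 31, or 32 if relaxation quality is counted separately. Stratified, uterus-volume and mixed-model analyses are not counted.

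**3. Chance of at least one P<.05 when no outcome differs.** For k independent tests this is 1 − 0.95^k. For a common correlation ρ between test statistics, with c = 1.96, it is

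1 − ∫ φ(u) [Φ((c − √ρ u)/√(1−ρ)) − Φ((−c − √ρ u)/√(1−ρ))]^k du.

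The document gives no ρ, so a range is shown.

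| k | ρ = 0 | ρ = 0.3 | ρ = 0.5 | ρ = 0.8 | Expected false positives (0.05k) |
|---|---|---|---|---|---|
| 9 (pain only) | 37.0% | 32.6% | 26.9% | 16.6% | 0.45 |
| 26 | 73.6% | 61.9% | 47.5% | 24.5% | 1.3 |
| 31 | 79.6% | 67.1% | 51.4% | 25.9% | 1.55 |

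The expected number does not depend on ρ.

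**4. A different correlation pattern.** Suppose outcomes correlate within domains only: for 26 tests, pain 9, movement 2, surgeon 4, stability 2, times 2, indirect costs 3 and four single outcomes, with independence between domains. The chance is then one minus the product of the domains' no-rejection probabilities. As within-domain ρ rises from 0.3 to 0.9, it falls from 71.0% to 52.4% for 26 tests and from 76.8% to 55.0% for 31.

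**5. Outcomes that may not be null.** Dropping direct costs leaves 25 of the 26: 1 − 0.95^25 = 72.3% if independent. Dropping additional blocking agent as well leaves 29 of the 31: 1 − 0.95^29 = 77.4%. The size of the problem barely changes.

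**The case against.** The strongest reply is that ordering, adjusting or labelling secondaries is SAP content, that a SAP is announced, and that the quoted sentence is boilerplate. The same paragraph provides for comparisons of more than two groups in a two-arm trial. It is true that the SAP could add a hierarchy or label. But the protocol has already stated a rule. A SAP that follows it inherits the problem, and one that restricts it departs from the protocol after 40 patients have been enrolled. The point therefore rests on what is written, not on missing detail.

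Other parts of the reply stand and limit the point:

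- A reader might infer that a false positive is more likely than not. The documents do not support that as a fact. Under a common correlation, the chance drops below one half once ρ exceeds about 0.47 for 26 tests or 0.52 for 31.
- A reader might infer that the trial's 5% error rate is broken. That rate is claimed for the main outcome only and is unaffected.
- The outcomes are labelled secondary, and no passage says that one of them may rescue a failed primary.
- The mixed-model sentence does not name the repeated overall pain scores. They fit its wording, but so do surgeon ratings, PONV and site-specific pain. A second test of the primary's raw data is a possible reading, not a stated plan.
- Drug cost and additional blocking agent are tied to the allocated regimen, so they are not plausible nulls. Tests on uncommon binary outcomes can run below their nominal size. That cost and quality-of-life items will be tested at .05 follows from the general rule and is not stated for each.

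**Conclusion.** The point holds as a matter of interpretation. The protocol gives every secondary comparison the same license to be called significant, and nothing in the text restrains it. With no true secondary differences, the chance of at least one false finding is about 25% to 74% for 26 tests and 17% to 37% for the nine pain outcomes. These ranges rest on an assumed common correlation of 0.8 to 0, on all the outcomes being null and on tests of exact 5% size, so they illustrate scale and do not predict. Even the lowest is more than three times 5%. The primary conclusion, the sample size and the conduct of the trial are not affected. The change is worth making, but the validity of the primary result does not depend on it.

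**What to change.** In the statistical methods section, keep the P<.05 threshold for the primary AUC t test and remove it from the general paragraph on group comparisons. Replacement wording could be: all secondary, mixed-model and stratified analyses, including those by uterus volume, are exploratory; they are reported as estimates with 95% CIs and, if given, nominal P values; they cannot support a claim of pain benefit if the primary test is not significant. Label Table 2 to match and carry the same text into the SAP.

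If the investigators want confirmatory secondaries, they may name a short list, tested with multiplicity control only after a significant primary. Which outcomes and which procedure are for them to choose.

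The cost is wording only: no patients, data or procedures change. The downside is that secondary results outside any such list can no longer be called significant.
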